## 10.1 Screening Examination

The screening examination will take place on the day of the screening visit. Subject data to be collected at the Screening Examination includes the following baseline measures: contact information questionnaire, demographics questionnaire, smoking-related medical history questionnaire, TSCP smoking history questionnaire, recent smoking history questionnaire, medication use and intolerance questionnaire, financial questionnaire, work break questionnaire, cost of smoking questionnaire, general health questionnaire, cancer questionnaire, self-efficacy questions, Fagerstrom Test for Nicotine Dependence (FTND), Mood and Physical Symptoms Scale (MPSS), Patient Health Questionnaire (PHQ-2 as well as PHQ-9 question 9), Generalized Anxiety Disorder-2 (GAD-2), Alcohol Use Disorders Identification Test (AUDIT-C), and the Perceived Stress Test (PSS-4). The subject will also complete a urine pregnancy test if female and of child-bearing potential.

The urine pregnancy test will be conducted by the CTA or other study staff with the appropriate training. Most information except the urine pregnancy test results will be documented in the EMR because these assessments are all part of standard clinical practice within the TSCP. If the screening visit occurs at the CSC, outside of the normal TSCP clinic, all information will be collected on paper forms or in REDCap. If the screening visit occurs at the TSCP during a routine clinic visit, the study Physician or Physician Assistant will review the visit documentation to assess eligibility. In the event of a screen failure, documentation of this will be noted in eResearch. Participants that fail the screening process will receive follow-up from the study physician to ensure the participant has been connected to appropriate clinical care.

**Enrollment/Randomization Visit:** If an individual meets the criteria to be enrolled in the study, they will be asked to come to the Enrollment/Randomization Visit. At this visit, the individual will be enrolled (given a study ID) and randomized to adaptive vs. non-adaptive treatment. The CTA will notify the research pharmacy of the enrollment and randomization status and will pick up medications/placebos for the participant then give these to the participant with a description of how to use them. The participant will then be scheduled for follow up visits in 2 weeks (Medication Response Visit) and 2- and 12-week post quit. They will also be entered into the phone-based follow up system (see Phone-based Assessment Time Table below). At the point of Enrollment, all payment for TSCP services will stop, and participants receive free treatment, medications etc. through the study.

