### 3 PROTOCOL SYNOPSIS AND RESEARCH SUMMARY

#### 3.1 Purpose

The purpose of this study is to assess an “adaptive” approach to smoking cessation pharmacotherapy. The protocol is designed to compare adaptive vs. standard approaches to two common smoking cessation pharmacotherapies (Varenicline and Nicotine Patch). The adaptive treatment approach provides the addition of Bupropion in the pre-quit period for participants who are not “responding” to initial treatment. Little is known about the adaptive use of Varenicline or Nicotine Patch, in which Bupropion is added to Varenicline or Patch for those who do not respond to one of these medications in a pre-quit treatment period. This study attempts to address these knowledge deficits. The study (N=300) is a double-blinded randomized placebo-controlled trial designed to compare biochemically-confirmed abstinence rates in smokers randomized to Varenicline Adaptive Protocol vs. Varenicline (N=150) and for comparison, Nicotine Patch Adaptive Protocol vs. Nicotine Patch (N=150). The “Varenicline Adaptive Protocol” is conducted by starting treatment with Varenicline 4 weeks prior to the quit day, then following each participant’s response to this pre-treatment medication. After 2 weeks, if the patient shows a reduction greater than 50% in cigarettes smoked per day then the patient is considered to be a “Varenicline responder” and is continued on Varenicline alone out to 12-weeks post quit day. If the patient does not spontaneously decrease smoking in the pre-quit period by more than 50% cigarettes per day, the patient is considered to be a “Varenicline non-responder” and Bupropion is added to the Varenicline. For comparison, an identical protocol is used with nicotine patch vs. nicotine patch adaptive treatment. The study uses only FDA-approved medications: Varenicline, Nicotine Patch, Bupropion, and placebo controls. To pattern clinical practice, participants will be able to choose whether they would like to use a patch or Varenicline-based treatment. After choosing, however, they will be randomized to adaptive vs. non-adaptive version of that treatment. Placebo medications are matched throughout the study. Participants will be blinded to all medications. All participants will receive behavioral treatment including a single 40-minute visit with a medical provider. The study is designed to provide researchers and clinicians with a better understanding of how to use adaptive pharmacotherapy protocols to improve smoking cessation rates.

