#### 7.1.5. Study Drug Blinding

Subjects are blinded to their active medications. Study personnel who are in contact with participants, including the CTA, study clinician, and PI, are blinded to active medication.

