### 8.2 Packaging and Labeling

All medications will be labeled according to Investigational Chemotherapy Service (ICS) Standard Operating Procedures to include at least: drug name/strength, quantity, lot number, and expiration or retest date. Placebo medications will be provided in non-descript packaging, similarly to non-placebo medications.

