### 8.3 Supply, Receipt, and Storage

Pfizer will provide Varenicline and placebo Varenicline; nicotine patches, bupropion and placebo bupropion will be provided by Central Compounding Pharmacy Incorporated. CVS brand clear adhesive bandages will be purchased to serve as placebo nicotine patches. For individuals who do not have an adhesive allergy, but instead have other forms of skin sensitivity such as discoloration, redness, tenderness (which can be related to the adhesive used in specific brands of patch), an alternate placebo or active patch will be purchased. This will provide an alternative for participants who express concerns about these types of issues but would like to continue using nicotine patch. ICS will be responsible for managing the receipt and storage of all pharmaceuticals and placebo medications.

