### 10.4 Follow-up Period

Following the End of Treatment, participants will receive two follow-up phone assessments (detailed further in section 10.7). These phone assessments will occur at 26-weeks post-TQD and 52-weeks post-TQD. If participants are not currently abstinent from tobacco at the End of Treatment, a referral to clinical resources within the TSCP will be offered.

**Follow up Study Assessment Visits:** At each assessment visit, there will be a standardized evaluation. The screening will be provided through the Duke Smoking Cessation Program for clinical purposes. Later assessments (Enrollment, Medication Response, 2- and 12-week post quit) will be provided by the CTA. During these visits there will be multiple self-report assessments (see below) as well as CO testing. Finally each participant will receive a total of 10 phone calls out to 1 year post quit attempt. Biochemically confirmed 30-day continuous abstinence at twelve weeks post-Target Quit Day is the primary endpoint to determine abstinence. Other endpoints, including biochemically confirmed 7-day point prevalent abstinence at two and twelve weeks post-TQD and self-reported abstinence rates via phone-based assessment up to 52-week post-TQD, will also assess abstinence as secondary measures.

**Phone-based Assessment Time Table:** The phone assessments function to collect data on study participants but also to check on difficulties with medications, medication side effects and to remind participants of upcoming visits. The timing is as follows:

|    |                                            |
|----|--------------------------------------------|
| 1  | 1 day after the Enrollment Visit           |
| 2  | 1 day before the Medication Response Visit |
| 3  | 1 day pre-TQD                              |
| 4  | 1 day post-TQD                             |
| 5  | 1-week post-TQD visit                      |
| 6  | 1 day before the 2-week post-TQD visit     |
| 7  | 6-week post-TQD time point                 |
| 8  | 1 day before the 12 week post-TQD visit    |
| 9  | 26 week post-TQD time point                |
| 10 | 52 week post-TQD time point                |

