### **11.3 Emergency Unblinding of Investigational Treatment**

Study staff in direct contact with participants (Clinical Trials Assistants, Study Clinician) will not be blinded to the selection of Varenicline or Nicotine Patch. All study staff in direct contact with participants will be blinded to the randomization to adaptive vs standard treatment algorithms. The Clinical Research Coordinator will have access to participant randomization for emergency un-blinding. In the case that Emergency un-blinding is required, the Principle Investigator will contact the Clinical Research Coordinator directly to obtain the necessary information. Emergency contact information for un-blinding will be the email and cell phone number of [name], the study CRC: [[contact]](mailto:[contact]); [contact].

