### **11.8 External Data and Safety Monitoring Board (DSMB)**

NIDA website describing the criteria for DSMB states “A Data and Safety Monitoring Board (DSMB) is generally required for Phase III clinical trials. For earlier medication trials (Phase I or II and some behavioral clinical trials), a DSMB may be appropriate if the study has multiple clinical sites, is blinded, tests a high-risk intervention, or is conducted in vulnerable populations.” According to these criteria, this study should not require a DSMB; it is not a Phase III clinical trial, does not use multiple clinical sites, is not blinded, does not test a high-risk intervention, and is not conducted in a vulnerable population.

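### Section 10.1 routes randomization status through the CTA, whom Sections 7.1.5 and 11.3 declare blinded and who also runs the 12-week primary-endpoint visit

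*Protocol*

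**What the plan says.** Protocol Section 7.1 calls the trial double-blinded. Two sections say whom the blind covers:

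- Section 7.1.5: "Study personnel who are in contact with participants, including the CTA, study clinician, and PI, are blinded to active medication".
- Section 11.3: "All study staff in direct contact with participants will be blinded to the randomization to adaptive vs standard treatment algorithms". The sentence before it names the Clinical Trials Assistants as staff in direct contact. The section gives access to the allocation to the Clinical Research Coordinator.

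Section 10.1, under the Enrollment/Randomization Visit, first says that the participant is randomized to adaptive or non-adaptive treatment. It then says: "The CTA will notify the research pharmacy of the enrollment and randomization status and will pick up medications/placebos for the participant". The CTA goes on to hand the product over.

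Section 10.4 gives the outcome visits to the same role: "Later assessments (Enrollment, Medication Response, 2- and 12-week post quit) will be provided by the CTA".

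Three other places bear on the blind:

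- Section 8.2 requires labels "to include at least: drug name/strength, quantity, lot number, and expiration or retest date". It adds that placebos come in plain packaging similar to that of the active products.
- Section 8.3: "CVS brand clear adhesive bandages will be purchased to serve as placebo nicotine patches". Active patches come from a compounding pharmacy. Section 3.1 says: "Placebo medications are matched throughout the study".
- Section 11.8 explains the absence of a DSMB by saying, among other things, that the study "does not use multiple clinical sites, is not blinded, does not test a high-risk intervention".

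**The concern.** Sections 7.1.5 and 11.3 state who is blinded. Section 10.1 describes a working procedure that, as worded, breaks this for the CTA. Staff follow procedures, so the procedure is likely to decide what happens.

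The role matters because the CTA conducts the Medication Response, 2-week and 12-week assessments. The primary endpoint in Section 6 has two parts: CO below 7 ppm and a single-item self-report of 30-day continuous abstinence. A CTA who knows the arm could put the self-report question differently, give different encouragement, or try harder to bring one arm back for the visit. Sections 13.3 and 13.4 count anyone lost after randomization as non-abstinent, so unequal retention effort feeds straight into the endpoint. Bias of this kind cannot be removed in the analysis.

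**Working it through.** The core of the point is a comparison of texts. The protocol has no figure to reproduce.

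**Step 1: what does the CTA learn?**

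| Place | Content |
|---|---|
| 7.1.5 | CTA blinded to active medication |
| 11.3 | Contact staff, CTAs included, blinded to adaptive versus standard; coordinator has access |
| 10.1, one sentence | Participant is given an ID and randomized to adaptive or non-adaptive |
| 10.1, next sentence | CTA reports enrolment and randomization status to the pharmacy, collects and hands over the product |

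Enrolment is listed separately from randomization status, and the preceding sentence has just given the two possible results of randomization. No kit number, coded assignment or pharmacy-held list is described. Section 7.1.6 names a public randomization website but not who runs it or keeps the list. The natural reading is that the CTA transmits the arm.

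**Step 2: does that role touch the primary endpoint?** Yes. Section 10.4 assigns the 12-week visit to the CTA, with self-report and CO testing, and Section 6 builds the endpoint from those two measurements.

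**Step 3: secondary routes.**

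- *Labels (8.2).* Name and strength are the stated minimum. Similar packaging is promised, but no wording says that the label is the same for active and placebo. The CTA handles the product at dispensing and again at the unused-medication counts (8.5).
- *Patch (8.3, 10.2).* Placebo and active patches come from different sources. In the patch standard arm (planned n = 75) participants use the bandage for four weeks and the active patch from the quit day, so the same person handles both in turn. This makes the matching statement in 3.1 doubtful for the patch stratum (planned n = 150).
- *DSMB (11.8).* The criteria quoted there list blinding as a circumstance in which a DSMB may be appropriate. The section then treats the study as not blinded, against 3.1 and 7.1.

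**Step 4: illustration of size.** Assume no true effect, a common rate of 23.4% (the control rate in the protocol's sample size section), 150 per arm, and a two-sided 5% pooled test of two proportions. Let recorded rates move by d/2 upward in one arm and d/2 downward in the other. The shifts are assumptions.

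SE under the null = √(2 × 0.234 × 0.766 / 150) = 0.0489. The critical difference is 1.96 × 0.0489 = 0.0958. The unpooled SE is 0.0488 for d = 4 points (25.4% v 21.4%) and also 0.0488 for d = 6 points (26.4% v 20.4%).

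- d = 4 points: Φ((0.04 − 0.0958)/0.0488) + Φ((−0.04 − 0.0958)/0.0488) = 0.127 + 0.003 = about 13%.
- d = 6 points: Φ((0.06 − 0.0958)/0.0488) + Φ((−0.06 − 0.0958)/0.0488) = 0.231 + 0.001 = about 23%.
- d = 2 points, by the same formula: 0.060 + 0.009 = about 7%.
- d = 0: 5%.

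Exact binomial calculation gives 13.0% and 23.3% for the 4- and 6-point shifts.

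**The case against.** The best defence is that randomization status may only mean that the person has been randomized. Two explicit statements say that the CTA is blinded, and one loosely worded sentence should not override them. This has some force: the sentence does not prove that the CTA sees the arm. But nothing in 10.1 limits it to the harmless sense, the preceding sentence points the other way, and no coded step is described. The wording must change on either reading.

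A second defence is that the CO criterion is objective. That stands, and it limits how far recorded abstinence can be moved. It does not cover the self-report item, support or retention.

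Several stronger readings are tempting, and the protocol does not support them:

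- *Allocation concealment is lost.* In 10.1 the notification comes after the participant is enrolled and randomized. The text shows at most a loss of blinding after assignment.
- *The CTA completes diaries by time-line follow-back and so settles responder status.* Section 10.7.5 gives that task to the RA, and only when the diary was not filled in. No section says that the diary determines response.
- *The labels reveal placebo.* A label with name and strength could still cover both active and placebo, and staff already know whether varenicline or patch was chosen (11.3). The defect is that 8.2 does not say the labels are blinded.
- *The placebo patch is visibly different.* The appearance of the active patch is not described. A difference is a plausible inference, no more.
- *The single-site statement in 11.8 is false.* Section 10 mentions six clinics as a recruitment network but also a central study site. The point is arguable and is not pressed.

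Finally, correcting 11.8 does not by itself require a DSMB. The quoted criteria are permissive, and Section 11.7 provides annual safety review.

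**Conclusion.** The concern holds as a contradiction in operative text. Section 10.1, read naturally, gives the arm to a role that 7.1.5 and 11.3 declare blinded and that collects the primary endpoint. It rests on reading randomization status as the arm, which the context favours but does not prove. The label and patch points are secondary: the protocol leaves the blind unsecured there but does not show that it fails. The statement in 11.8 that the study is not blinded is wrong on the protocol's own terms.

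A reader might infer that the double blind is certain to fail by three separate routes. The documents do not go that far.

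The size of any bias is unknown. The error rates of about 13% and 23% follow from assumed net shifts of 4 and 6 points that need opposite movement in the two arms. With smaller shifts the rate falls back toward 5%. They show sensitivity and are not estimates for this trial. The fix is still worth making before enrolment proceeds, since lost blinding cannot be restored later.

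**What to change.** - **10.1:** State that the CTA sends the pharmacy only the study ID, the chosen drug, baseline cigarettes per day and, after the Medication Response Visit, the response data. Send the response data for every participant in both arms, so that sending them reveals nothing. The pharmacy, or the coordinator named in 11.3, holds the allocation and determines whether active or placebo product is dispensed under the protocol. Say in 7.1.6 who generates and keeps the list.
- **8.2:** State that labels are coded and do not distinguish active from placebo.
- **8.3 and 3.1:** Confirm that the placebo patch matches the active patch in appearance. If it does not, stop describing the patch stratum as double-blind.
- **11.8:** Correct the statement that the study is not blinded, and reconsider the DSMB conclusion on the correct premise.

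The cost is wording and pharmacy procedure. Only a matched placebo patch, if one is needed, has a purchase cost. Sample size, visits and endpoint are unchanged.

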## 10.2 Treatment Period

The following is an overview of active treatments and then active and placebo treatments for participants allocated to adaptive therapy and standard therapy groups:

**Figure 2. Adaptive Pharmacotherapy Protocol (n=150)**

|                                                                                                                                                                                                                                               |                                                                                                                                                                                                                                                        |
|-----------------------------------------------------------------------------------------------------------------------------------------------------------------------------------------------------------------------------------------------|--------------------------------------------------------------------------------------------------------------------------------------------------------------------------------------------------------------------------------------------------------|
| VARENICLINE-BASED TREATMENT
Participant chooses Varenicline-based treatment and is then randomized to Adaptive Treatment arm (N=75)                                                                                          | NICOTINE PATCH-BASED TREATMENT
Participant chooses Nicotine patch-based treatment and is then randomized to Adaptive Treatment arm (N=75)                                                                                             |
| VARENICLINE NON-RESPONDER
4 weeks prior to TQD: Start Varenicline
2 weeks prior to TQD, DOES NOT reduce cigs/day by > 50%
1 week prior to TQD: Start Bupropion
Use Varenicline + Bupropion to 12 weeks post TQD     | NICOTINE PATCH NON-RESPONDER
4 weeks prior to TQD: Start Nicotine Patch
2 weeks prior to TQD, DOES NOT reduce cigs/day by > 50%
1 week prior to TQD: Start Bupropion
Use Nicotine Patch + Bupropion to 12 weeks post TQD     |
| VARENICLINE RESPONDER
4 weeks pre-TQD: Start Varenicline
2 weeks prior to TQD - DOES reduce cigs/day by > 50%
1 week prior to TQD: Start Placebo Bupropion
Use Varenicline + Placebo Bupropion to 12 weeks post TQD | NICOTINE PATCH RESPONDER
4 weeks pre-TQD: Start Nicotine Patch
2 weeks prior to TQD - DOES reduce cigs/day by > 50%
1 week prior to TQD: Start Placebo Bupropion
Use Nicotine Patch + Placebo Bupropion to 12 weeks post TQD |

**Standard Treatment Regimens:** Participants who chose either Varenicline or Patch-based treatment but who are randomized to standard treatment will be given Varenicline or Nicotine Patch with what is now considered standard-of-care treatment. Varenicline Standard Treatment arm will start Varenicline 1 week prior to the TQD and continue for 12 weeks post TQD. Nicotine Patch Standard Treatment arm will start nicotine patch on the TQD and continue for 12 weeks post TQD. Placebo medications are used to match Adaptive Treatment Protocols and shown in Figure 3.

**Figure 3. STANDARD PHARMACOTHERAPY PROTOCOLS (n=150)**

|                                                                                                                                                                                                                                                              |                                                                                                                                                                                                                                               |
|--------------------------------------------------------------------------------------------------------------------------------------------------------------------------------------------------------------------------------------------------------------|-----------------------------------------------------------------------------------------------------------------------------------------------------------------------------------------------------------------------------------------------|
| VARENICLINE-BASED TREATMENT
Participant chooses Varenicline-based treatment and is then randomized to Standard Treatment arm (N=75)                                                                                                         | NICOTINE PATCH-BASED TREATMENT
Participant chooses Nicotine patch-based treatment and is then randomized to Standard Treatment arm (N=75)                                                                                    |
| VARENICLINE STANDARD TREATMENT
4 weeks pre-TQD: Start Placebo Varenicline
1 week prior to TQD – Switch to Active Varenicline
1 week prior to TQD: Start Placebo Bupropion
Use Varenicline + Placebo Bupropion to 12 weeks post TQD | NICOTINE PATCH STANDARD TREATMENT
4 weeks pre-TQD: Start Placebo Nicotine Patch
TQD - start Nicotine Patch
1 week prior to TQD: Start Placebo Bupropion
Use Nicotine Patch + Placebo Bupropion to 12 weeks post TQD |

